**Fig. 3 Fig3:**
[figure not shown]
Time-to-event figure for day 14 mortality. The number of people at risk in each group will be listed for days 0, 7 and 14. Cox regression analysis with random effect for site and fixed effects for the exposure adjusted for the time between T0 (initiation of vasopressor therapy) and randomisation, vasopressor dose, APACHE III score at randomisation and type of shock will be usedRRT-free days by day 28 will be defined as the number of days in the first 28 days post-randomisation when the participant was alive and not dependent on RRT. RRT-free days by day 28 will be analysed as an ordinal outcome, with death assigned the worst value (− 1). Comparisons between groups will be made using a mixed effects proportional odds regression model, with the same fixed and random effects as per the primary outcome model.

### Safety events

For new adverse events within 28 days, counts and percentages will be reported with *P*-values using Fisher’s exact test where one or more expected count is < 5 or Pearson’s chi-square test, otherwise (Table 5). Win ratio, which is a relatively new approach, appears to be more useful in analysing composite endpoints with varying degree of severity [20] and is increasingly being used as seen in recent RCTs [21, 22]. The win ratio will be calculated by comparing each patient in the treatment group with each patient in the control group to determine who “wins” based on predefined criteria. It provides a hierarchical assessment by first considering the most critical outcomes, such as mortality, before less critical ones, such as adverse events [20]. Hierarchical endpoint in this trial would be a combination of mortality, haemorrhagic stroke, ischemic stroke, cardiac arrest, myocardial ischemia, mesenteric ischemia, renal failure requiring RRT, ventricular arrhythmia, bilateral digital ischemia, takotsubo cardiomyopathy and atrial arrhythmia. Additionally, a sensitivity analysis for the win ratio will be performed using an alternative hierarchy of outcomes using the following order: death, cardiac arrest, ventricular arrhythmia, haemorrhagic stroke, ischaemic stroke, myocardial ischaemia, mesenteric ischaemia, renal failure requiring RRT, bilateral digital ischaemia, Takotsubo cardiomyopathy and atrial arrhythmia. This analysis will assess the robustness of above findings to different event ordering. In addition to win ratio, the net benefit—which is the difference in the proportion of wins between the two groups—will also be reported.

**Table 5 Tab5:** Adverse events (*N*,%) accrued in hospital within 28 days

	Standard MAP	Individualised MAP	*P* value
Hospital mortality			
Haemorrhagic stroke			
Ischemic stroke			
Cardiac arrest			
Myocardial ischemia			
Mesenteric ischemia			
Renal failure requiring RRT			
Ventricular arrhythmia			
Bilateral digital ischemia			
Takotsubo cardiomyopathy			
Atrial arrhythmia			
Hierarchical composite of above events	Win ratio (95% CI): Net benefit (95% CI):		

*RRT* renal replacement therapy

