### Objectives

The aim of the REACT SHOCK RCT is to determine effectiveness and safety of a strategy, where MAP target during vasopressor therapy for shock in ICU is individualised based on patient’s own pre-illness MAP that would be derived as an average of up to five (and at least two) most recent pre-illness blood pressure readings from within the last 3 years. Our primary objective is to determine whether an individualised MAP target strategy can improve 14-day all-cause mortality compared to standard blood pressure targets among patients with shock. Secondary objectives are to determine whether individualised MAP targets can improve 90-day all-cause mortality, major adverse kidney events by day 14 (MAKE-14), time to death from randomisation to day 14 and day 90, peak increase in serum creatinine, and days alive and free of renal replacement therapy (RRT) by day 28. Safety will be assessed by comparing new adverse events between the two groups.

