### Primary outcome

Effect estimates for 14-day all-cause mortality will be derived from multivariable logistic mixed effects models with a random intercept for site (assumed normally distributed on the logit scale, with a constant variance) to account for clustering within sites and fixed effects for treatment group, time between T0 (initiation of vasopressor therapy) and randomisation, APACHE III score at randomisation, noradrenaline-equivalent dose at randomisation and type of shock (Table 4). A two-sided *P*-value for the effect of treatment will be obtained from this model and values < 0.05 will be considered statistically significant. The effect estimates of interest will be the relative risk and risk difference (individualised care versus standard care). The relative risk estimate will be obtained as a ratio of the mean for each group of the individual predicted probabilities obtained from the logistic regression model. Differences of these means will be the risk difference. Bootstrapping, using 10,000 iterations, will be used to calculate 95% confidence intervals.

**Table 4 Tab4:** Outcome measures

	Standard MAP (*n* = xxx)	Individualised MAP (*n* = xxx)	Adjusted^*^ relative risk (95% CI)	Adjusted^*^ risk difference (95% CI)	*P* value
Day 14 all-cause mortality, *n* (%)					
Major Adverse Kidney Event^δ^ within 14 days of randomisation, *n* (%)					
- New requirement for RRT					
- Doubling of creatinine					
RRT- free days^#^ by day 28, *n* (%)					
Day 90 all-cause mortality, *n* (%)					

*RRT* renal replacement therapy

^*^ The model included random intercepts for sites and fixed effects for treatment group, the time between T0 (initiation of vasopressor therapy) and randomisation, APACHE III score at randomisation, vasopressor dose at randomisation and type of shock

^**δ**^ Major adverse kidney event (MAKE)−14 was a composite outcome of death, or new renal replacement therapy during the first 14 days, or doubling of serum creatinine from pre-illness level on day 14 or on day of discharge from ICU, whichever was earlier

^#^ Patients who died were assigned the worst score of − 1

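### Table 5 plans only counts, percentages and a P value for each adverse event; each row needs an effect estimate with a confidence interval

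*Protocol article*

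**What the plan says.** The Objectives section of the protocol article puts safety in the trial's aim: "The aim of the REACT SHOCK RCT is to determine effectiveness and safety of a strategy". It also says how this will be done: "Safety will be assessed by comparing new adverse events between the two groups".

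The Safety events section under Statistical methods then fixes the method for single events: "For new adverse events within 28 days, counts and percentages will be reported with *P*-values using Fisher’s exact test". That test is reserved for small expected counts (under 5); every other comparison uses Pearson's chi-square. The Table 5 shell, titled "Adverse events (*N*,%) accrued in hospital within 28 days", has one column per arm and one for the P value. Its only row with an estimate is the last, the hierarchical composite: "Win ratio (95% CI): Net benefit (95% CI").

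Table 4 is laid out differently. Its columns are an adjusted relative risk and an adjusted risk difference, each with a 95% interval, plus a P value. Its rows include day-14 and day-90 mortality and "New requirement for RRT" within the day-14 kidney composite.

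The Sample size section bases the 1260 patients on 14-day mortality alone. No adverse event rate appears anywhere in the article.

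**The concern.** The Introduction accepts that an individualised target may lead to more vasopressor use, so harm is a plausible cost of the strategy and the per-event comparison matters. For a pressure-target trial, the safety question is how much extra harm the data leave open. A count, a percentage and a P value do not answer that. The size of the difference is left for the reader to work out, and its precision is not shown.

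This matters most for uncommon events. A trial sized for a six-point mortality difference has little chance of a small P value when a rare harm doubles. A row of non-significant values would then be the expected result whether or not harm exists, and the planned table would not let a reader tell the two situations apart.

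**Working it through.** **1. The plan's own sample size.** Inputs (Sample size section): 20% control mortality, 6-point reduction (so 14%), alpha 0.05, power 80%, attrition 2.5%. Two-sided testing is taken from the Primary outcome section. Pooled normal formula without continuity correction:

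n per arm = [1.96 × √(2 × 0.17 × 0.83) + 0.842 × √(0.20 × 0.80 + 0.14 × 0.86)]² / 0.06² = 614.1, rounded up to 615.

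Total 1230; 1230 / 0.975 = 1262. The stated 1260 reproduces. It rests on mortality only; no safety event enters it.

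**2. What the planned tests can detect.** With 1:1 allocation there are 630 per arm. The expected count in each arm is half the total number of events, so the plan's rule uses Fisher's test below 10 events in total and Pearson chi-square otherwise. Two-sided 0.05 is assumed, because the article states no level for safety tests. The power for a doubling was enumerated exactly:

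Power = Σₐ Σ_b Bin(a; 630, p) × Bin(b; 630, 2p) × 1{planned test gives P < 0.05 and b > a}.

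The control rate p is an assumption, so a range is shown.

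| Control rate → doubled rate | Power | Doubling missed |
|---|---|---|
| 0.5% → 1% | 12% | 88% |
| 1% → 2% | 31% | 69% |
| 1.5% → 3% | 44% | 56% |
| 2% → 4% | 56% | 44% |
| 3% → 6% | 74% | 26% |
| 4% → 8% | 86% | 14% |
| 5% → 10% | 93% | 7% |

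Hand check at 1% → 2% by normal approximation: the null standard error is √(2 × 0.015 × 0.985 / 630) = 0.00685 and the alternative standard error is √((0.0099 + 0.0196) / 630) = 0.00684. Then (0.01 − 1.96 × 0.00685) / 0.00684 = −0.50, and Φ(−0.50) = 0.31, in agreement. By the same approximation, power passes 50% at a control rate of about 1.8% and 80% at about 3.5%. With 614 per arm after attrition, the exact powers fall by about 1 point or less.

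**3. What an interval would add.** Illustrative counts, 630 per arm, standard v individualised. The relative-risk interval is exp(ln RR ± 1.96 × √(1/a − 1/630 + 1/b − 1/630)). The risk-difference interval is Newcombe's, built from score limits.

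| Events | P | Relative risk (95% CI) | Risk difference, points (95% CI) |
|---|---|---|---|
| 6 v 6 | 1.00 | 1.00 (0.32 to 3.08) | 0.00 (−1.22 to +1.22) |
| 6 v 12 | 0.15 | 2.00 (0.76 to 5.30) | +0.95 (−0.42 to +2.44) |
| 13 v 22 | 0.12 | 1.69 (0.86 to 3.33) | +1.43 (−0.43 to +3.37) |

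For 6 v 12: √(1/6 + 1/12 − 2/630) = 0.497, and exp(0.693 ± 0.974) gives 0.76 to 5.30. All three rows are non-significant, but the excess that they leave open runs from about 1.2 to 3.4 points. The P-value column does not show that.

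**4. Whether the composite fills the gap.** Take the design mortality rates (20% v 14%) as the top tier and one lower-ranked event, assumed independent of death.

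- Event at 1% in both arms: wins are 0.86 × 0.20 + 0.688 × 0.01 × 0.99 = 0.1788 and losses are 0.14 × 0.80 + 0.688 × 0.01 × 0.99 = 0.1188, where 0.688 = 0.86 × 0.80. Win ratio 1.51.
- Event doubled to 2% in the individualised arm: wins are 0.172 + 0.688 × 0.01 × 0.98 = 0.1787 and losses are 0.112 + 0.688 × 0.02 × 0.99 = 0.1256. Win ratio 1.42.

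The composite still clearly favours the intervention, and nothing in it identifies the doubled harm.

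**The case against.** The best defence is that this is a presentation matter. Counts and percentages are printed, so anyone can compute a crude difference and interval. Safety does not rest on P values alone: the win ratio and net benefit carry intervals, severity and causality are assessed for each event, and the steering team and the DSMB review accrued events. Death and new renal replacement therapy already have estimates with intervals in Table 4. Adding intervals does not raise power, and the article never promised power for single harms.

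Much of this stands. Nothing here biases an estimate or touches the primary conclusion, and the miss rates show why a bare P value informs little, not something that the fix would cure. It does not remove the point. The composite is led by death, and Table 4 uses other time windows (days 14 and 90, against in hospital within 28 days). Nine of the ten prespecified events besides death have no planned estimate at all. Since text and table shell both specify the method, this is a stated choice and not a detail left for later.

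A reader might infer two stronger things that the documents do not support. One is that the plan treats a non-significant result as safe. It states no interpretation rule for adverse events; the 0.05 threshold is given for the primary model. The other is that most of the listed harms would be missed. Without event rates that cannot be said, and at control rates of 4% or more the planned tests have over 85% power for a doubling.

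**Conclusion.** The point holds as a limited one. For single adverse events the plan fixes a test without an estimate or interval, although safety is a stated aim and Table 4 shows that the authors report estimates elsewhere. For events with control rates up to about 2%, a non-significant P value is weak information: a true doubling would be missed 44% to 88% of the time across assumed rates of 2% down to 0.5%. For commoner events the problem fades (7% missed at 5%). These figures assume 630 per arm, two-sided 0.05 and event rates that the article does not supply, so they are illustrations, not predictions for named events.

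It does not follow that P values must go, or that safety should be read from an upper confidence limit. No margin is defined, and even equal counts of 6 v 6 give an upper relative-risk limit of 3.08, so such a rule would hardly ever reassure for a rare event.

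**What to change.** In the Safety events section and in Table 5, add for each event the risk difference, the relative risk or both (individualised versus standard), with a 95% interval suited to rare events, for example a score interval. The P-value column may stay. Add one sentence stating that P > 0.05 for an adverse event is not evidence of no harm.

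The cost is a wider table and slightly more analysis. No new data or patients are needed, and since the article reports that recruitment is still under way, the change can be made before results are known.

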## Methods: participants, interventions and outcomes

### Trial design and study setting

The REACT SHOCK RCT is an investigator-initiated, pragmatic, international, multicenter, open-label, parallel-group, randomised, standard-care controlled, clinical superiority trial among 1260 critically ill patients, who will be recruited at up to 35 ICUs in Australia, Ireland, Singapore, UK and USA. The trial will be conducted in accordance with Good Clinical Practice guidelines and comply with the principles of the Declaration of Helsinki, national and international regulatory requirements and general data protection regulations. The study is prospectively registered in public registries (ANZCTRN 12623000044628; ClinicalTrials.gov ID NCT05850962) and a pre-specified statistical analysis plan is published here.

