### Randomisation

Randomisation will be undertaken centrally in a concealed fashion, with a unique computer-generated, site stratified, permuted block randomisation method with random block sizes of 4 and 6. Enrolled patients will be randomly allocated in a 1:1 ratio to either standard care arm or intervention arm.

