### Sample size

Based on our pilot feasibility study [11] and prospective cohort study [8], a sample size of 1260 is required to demonstrate an absolute risk reduction of 6% in the primary endpoint (14-day mortality) in the intervention arm, assuming a 20% incidence of 14-day mortality in the control arm, at an alpha level of 0.05 and power of 80% and allowing for 2.5% attrition. The absolute risk difference of 6% is a conservative estimate relative to the effect size observed in our feasibility study (14-day mortality rate of 13% versus 6% in the standard care versus individualised blood pressure target) [11] or the effect size observed in a pre-specified comparative analysis in our prospective cohort study (14-day mortality rate of 13% versus 22% (*p* = 0.04) in the group with lower-than-median blood pressure deficit versus the group with higher-than-median blood pressure deficit) [8].

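### Adverse events are tested without the site strata used in randomisation, so the pooled Pearson test is slightly conservative for the more common events

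*Protocol article*

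**What the plan says.** Under Randomisation, the protocol article specifies a "site stratified, permuted block randomisation method with random block sizes of 4 and 6", with 1:1 allocation. Site is the only stratification factor named.

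Under Primary outcome, the 14-day mortality model is fitted "with a random intercept for site". The Secondary outcomes section applies the same model to 90-day mortality and MAKE-14, puts a random effect for site in the Cox model, and gives the RRT-free-days model the same fixed and random effects as the primary model. The models under Treatment separation between the two arms include site as a fixed effect.

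Under Safety events, counts and percentages within 28 days are reported with P-values from Fisher's "exact test where one or more expected count is" below 5, and from Pearson's chi-square test in all other cases. Neither test has a term for site. Table 5 lists the rows to be tested, among them hospital mortality and renal failure requiring RRT.

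**The concern.** Blocking within site forces the arms to be nearly balanced at every site. Differences between sites in event rates then cannot contribute much to the difference between arms. The pooled Pearson test does not know this: it computes its variance as if all 1260 patients had been randomised in one group, so the between-site share stays in the error term. The standard error is too large, and the test rejects less often than its nominal level.

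For a safety comparison, that direction means a real excess of events is detected slightly less often. Some site variation is plausible. The trial recruits at up to 35 ICUs in five countries, and the Safety assessment section has local staff collect events from records and from talks with treating clinicians, with the local investigator assessing severity and causality. The plan is also uneven: Table 4 puts mortality and new RRT under site-adjusted columns, while Table 5 tests related outcomes with no site term.

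**Working it through.** **1. The plan's own figure.** The article states no power or error rate for the adverse-event tests. Its only relevant figure is the sample size of 1260 (20% v 14%, two-sided 0.05, 80% power, 2.5% attrition). With the mean rate 0.17:

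n per arm = [1.960 × √(2 × 0.17 × 0.83) + 0.842 × √(0.20 × 0.80 + 0.14 × 0.86)]² / 0.06² = (1.041 + 0.446)² / 0.0036 ≈ 614.1, so 615.

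The total is 1230, and 1230 / 0.975 = 1261.5, so 1262. The stated 1260 is reproduced and is not affected by this point.

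**2. Where each planned test applies.** With 630 per arm, the smaller expected count is 630 × T / 1260 = T / 2, where T is the total number of events. It is below 5 only if T < 10, that is, below 10 / 1260 = 0.8% overall. Pearson's test covers everything more frequent.

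**3. Size by formula.** Let ρ be the share of outcome variance that lies between sites. With arms balanced within site, the pooled statistic is about √(1 − ρ) times the stratified one. The pooled test therefore rejects only when the stratified Z exceeds c = 1.960 / √(1 − ρ). Its true level is 2 × [1 − Φ(c)]. Where the stratified test has 80% power (mean of Z 2.802), the pooled power is Φ(2.802 − c).

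The site standard deviations (SD, logit scale) and event rates below are assumptions.

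| Site SD | Event rate | ρ | c | Level | Power (stratified 80%) |
|---|---|---|---|---|---|
| 0.5 | 1% | 0.0028 | 1.963 | 5.0% | 79.9% |
| 0.5 | 15% | 0.0315 | 1.992 | 4.6% | 79.1% |
| 0.5 | 30% | 0.0484 | 2.009 | 4.5% | 78.6% |
| 0.8 | 1% | 0.0085 | 1.968 | 4.9% | 79.8% |
| 0.8 | 15% | 0.0777 | 2.041 | 4.1% | 77.7% |
| 0.8 | 30% | 0.1104 | 2.078 | 3.8% | 76.5% |

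**4. Size by simulation.** Setting: 35 equal sites of 36 patients (1260 / 35), blocks of 4 and 6 within site, normal site effects on the logit scale, 20,000 trials per scenario. The planned Fisher/Pearson rule is compared with a site-stratified Cochran-Mantel-Haenszel (CMH) test without continuity correction.

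Power, planned rule v CMH:

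| Event rates | SD 0.3 | SD 0.5 | SD 0.8 |
|---|---|---|---|
| 1% v 3% | 74.7 v 74.5 | 73.9 v 73.9 | 73.3 v 73.6 |
| 2% v 5% | 84.2 v 84.2 | 83.7 v 83.8 | 83.7 v 84.2 |
| 5% v 9% | 79.9 v 80.0 | 79.6 v 79.8 | 80.6 v 81.7 |
| 15% v 21% | 79.4 v 79.7 | 80.1 v 81.0 | 79.8 v 82.2 |
| 30% v 37.5% | 81.3 v 81.8 | 81.0 v 82.2 | 82.0 v 84.9 |

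Rejection with no effect, Pearson v CMH, at SD 0.5: 4.7% v 5.1% (15% rate) and 4.4% v 4.9% (30%). At SD 0.8: 4.5% v 5.1% (15%) and 3.9% v 5.1% (30%). These are close to the formula.

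A separate run of 20,000 trials for 15% v 20.5% gave 72.4% v 73.5% at SD 0.5 and 73.0% v 75.6% at SD 0.8.

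**5. The rarest events.** At a 0.5% rate with no effect, the planned rule rejects 2.1 to 2.3% of the time. Unstratified Pearson on the same data rejects 4.6 to 4.9%, and CMH 4.5 to 5.0%. The two asymptotic tests agree, so this conservatism comes from the discreteness of Fisher's test, not from leaving out site.

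**The case against.** The strongest case against is that simple pooled tests are a valid, slightly conservative choice for a descriptive safety table, and that the rest is preference. Much of this stands:

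- **Rare harms are hardly touched.** A reader might infer that power is lost mainly where harms are hardest to detect. The figures show the opposite: ρ shrinks with the event rate, and the loss is smallest for the rarest events. Any event rare enough for Fisher's test is tested the same way after the fix.
- **No level or decision is missed.** A reader might also infer that the tests fall short of a stated significance level, or that a stopping decision could turn on them. The 0.05 threshold in the article belongs to the primary model. The Safety events section sets none, and under Interim analyses the DSMB makes a consensus recommendation after reviewing safety events.
- **The larger figures need wide site variation.** At SD 0.8, a median rate of 15% implies a 95% range across sites of about 4% to 46%; at SD 0.5 it is about 6% to 32%.
- **Death and RRT are partly covered.** Site-adjusted models already handle 14-day and 90-day mortality, MAKE-14 and RRT-free days, though over windows that differ from Table 5.

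What does not stand is that nothing is left to improve. The test is fixed in the text and differs from how every other between-arm model treats site. The change is nearly free. The design assumes 20% control-arm mortality by day 14, so the hospital mortality row of Table 5 may well fall in the range where the loss is visible.

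**Conclusion.** The point holds as a minor one. The adverse-event tests leave out the only factor the trial stratifies by, and Pearson's test is slightly conservative as a result. For events at 15 to 30%, the power lost is 0.3 to 0.5 points at a site SD of 0.3, 0.9 to 1.2 at 0.5, and 2.3 to 2.9 at 0.8. For events governed by Pearson's test at 5% or below, it is about 0.3 points or less at SD 0.3 to 0.5 and at most about 1.1 at 0.8. If rates do not differ by site, there is no loss.

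These sizes rest on assumed event rates, assumed site SDs and equal site sizes. This is a refinement in the use of the design, not a material power defect.

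**What to change.** In the Safety events section, replace Pearson's chi-square test with the Cochran-Mantel-Haenszel test stratified by site, without continuity correction. Keep Fisher's exact test when any expected count in the pooled, all-site 2x2 table is below 5.

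The word pooled needs to be written in. With 18 patients per arm per site, even a 15% event has an expected count of 18 × 0.15 = 2.7 per arm, so a per-site reading would send common events to the exact test.

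The change needs no new data and uses a standard procedure in the software the article names. Recruitment is still under way, so it can be made before database lock. The cost is that Table 5 will mix stratified and unstratified P-values, so a footnote should mark which rows use which test. Sites with no case of an event add nothing to its stratified test, which does no harm.

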### Outcomes

The primary outcome is 14-day all-cause mortality. Mortality will be a binary variable, with mortality defined as a record of death within 14 days after randomisation.

Secondary outcomes (Table 3) are:90-day all-cause mortality: All-cause mortality from randomisation to day 90.Time to death through day 14: Time to death (hours) will be calculated as the difference between the date and time of death and the date and time of randomisation if death occurs within 14 days of randomisation. Where exact time of death is not available, time will be assumed as 12:00 on the date of death.Time to death through day 90: Time to death (days) will be calculated as the difference between the date of death and the date of randomisation.Major Adverse Kidney Event (MAKE-14): MAKE-14 is defined as a composite measure of death, new initiation of RRT, or doubling of serum creatinine from the premorbid level at day 14 [13, 14]. Individual components of MAKE-14 will also be reported. The premorbid serum creatinine level will be sourced as the latest available value from medical records within the last year before hospital admission or, if this value was unavailable, as the latest available value during the hospital stay at least 7 days before ICU admission. When neither of these are available, the premorbid serum creatinine will be estimated following the Kidney Disease: Improving Global Outcome (KDIGO) guidelines as described previously [15].Renal Replacement therapy (RRT) free days until day 28: Number of days from randomisation to day 28 where the participant is both alive and not dependent on RRT. Patients who die within 28 days will be assigned the worst score of − 1.

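### The only pooled safety analysis is a death-first win ratio, so a mortality benefit offsets non-fatal harms and the row cannot show absence of non-fatal harm

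*Protocol article*

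**What the plan says.** The Objectives section of the protocol article sets the safety question: "Safety will be assessed by comparing new adverse events between the two groups". The Safety events section answers it in two ways. First, each new adverse event within 28 days is tabulated by arm with a P value. Second, the events are pooled in a win ratio, reported with net benefit as the closing row of Table 5. Of the win ratio the article says: "It provides a hierarchical assessment by first considering the most critical outcomes, such as mortality, before less critical ones, such as adverse events".

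Mortality heads the hierarchy, followed by ten non-fatal events from haemorrhagic stroke down to atrial arrhythmia. One sensitivity analysis uses a second order: death stays first, cardiac arrest and ventricular arrhythmia move above the strokes, and the last three tiers stay where they were. Its purpose is given as: "This analysis will assess the robustness of above findings to different event ordering". The article describes no composite restricted to non-fatal events.

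Mortality is also the efficacy target. The Outcomes section states: "The primary outcome is 14-day all-cause mortality". The Sample size section is built on lowering it: "a sample size of 1260 is required to demonstrate an absolute risk reduction of 6% in the primary endpoint (14-day mortality) in the intervention arm".

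**The concern.** A pooled safety measure is useful because rare events have little power row by row, and a broad moderate increase shows best when they are combined. Here the combination includes the outcome that the trial hopes to improve, and ranks it first. If the intervention lowers mortality, each pair in which only the control patient died counts as a win in the safety row, whatever happens to the non-fatal events. The Background section names increased vasopressor use as a possible cost of the intervention, so non-fatal harm in the individualised arm is a live possibility.

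At stake is the interpretation of one row. A win ratio near or above 1 could be read as no excess of adverse events when it reflects fewer deaths offsetting more non-fatal events. The planned sensitivity analysis cannot separate the two, since death leads both orders.

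**Working it through.** **Inputs from the article.** Control mortality comes from "assuming a 20% incidence of 14-day mortality in the control arm". The target reduction of 6 points gives 14% in the individualised arm. Error rates and attrition come from "at an alpha level of 0.05 and power of 80% and allowing for 2.5% attrition". The test is two-sided ("A two-sided *P*-value for the effect of treatment will be obtained from this model and values < 0.05 will be considered statistically significant"), and 1:1 allocation of 1260 gives 630 per arm. The article gives no non-fatal event rates, so all of those below are assumptions.

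**The plan's own figure.** With pooled variance under the null and mean rate 0.17, n per arm = [1.96 × √(2 × 0.17 × 0.83) + 0.8416 × √(0.20 × 0.80 + 0.14 × 0.86)]² / 0.06² = 614.1, rounded up to 615. That is 1230 in total, and 1230 / 0.975 = 1262 after attrition. The stated 1260 reproduces, so 20% v 14% is the right design point.

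**Death tier alone.** These 14-day design rates stand in for the mortality tier, which in Table 5 is hospital mortality within 28 days.
- Win for the individualised arm (control patient dies, individualised patient survives): 0.20 × 0.86 = 17.2% of pairs.
- Loss: 0.14 × 0.80 = 11.2% of pairs.
- Difference: 6.0 points; win ratio from this tier 17.2 / 11.2 = 1.54.
- Both survive, so that lower tiers can decide: 0.80 × 0.86 = 68.8% of pairs.

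**Break-even in a two-tier model** (death, then any non-fatal event among survivors at rate a in control and b in the individualised arm). Wins minus losses = 0.06 − 0.688 × (b − a). This is zero when b − a = 0.06 / 0.688 = 8.7 points, whatever the baseline: 5% to 13.7%, 10% to 18.7%, 20% to 28.7% or 30% to 38.7%. If mortality is 20% v 17%, it is 0.03 / (0.80 × 0.83) = 4.5 points.

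**Worked cases, 630 per arm, delta-method 95% CI.**

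| Death, control v individualised | Non-fatal among survivors | Win ratio (95% CI) | Non-fatal tier alone |
|---|---|---|---|
| 20% v 14% | 10% v 10% | 1.34 (1.06–1.71) | 1.00 |
| 20% v 14% | 10% v 15% | 1.12 (0.89–1.42) | 0.63 |
| 20% v 14% | 10% v 17% | 1.05 (0.84–1.32) | 0.54 |
| 20% v 20% | 10% v 15% | 0.87 (0.70–1.09) | 0.63 |

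For the second row, wins are 0.172 + 0.688 × 0.10 × 0.85 = 0.2305 and losses 0.112 + 0.688 × 0.15 × 0.90 = 0.2049. A direct comparison of non-fatal events there gives p = 0.0045 over all randomised patients (8.0% v 12.9%), or p = 0.015 among survivors.

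**Eleven tiers, both stated orders.** Assumed control rates among survivors, independent: haemorrhagic stroke 0.5%, ischaemic stroke 1%, cardiac arrest 2%, myocardial ischaemia 2%, mesenteric ischaemia 1%, RRT 10%, ventricular arrhythmia 3%, digital ischaemia 1%, Takotsubo 0.5%, atrial arrhythmia 12%. With every event except RRT 1.5 times higher in the individualised arm, the win ratio is 1.008 in the main order and 1.004 in the alternative order. Without death it is 0.73 and 0.72.

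**Simulated trials** (630 per arm, 20% v 14% death, several sets of assumed rates).
- No non-fatal difference: win ratio 1.19 to 1.27, significantly favouring the individualised arm in 51% to 61% of trials.
- All non-fatal events × 1.5 at lower rates (any event about 18% to 19%): significant harm in 2% to 2.5% of trials, against 90% to 93% for a non-fatal composite.
- The same increase at higher rates (any event about 37% in one set): significant harm in 26% to 34%, against about 99%.

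**The case against.** The strongest reply is that the safety objective is already met by the per-event comparison: Table 5 has ten non-fatal rows, each with a P value. The article never calls the win ratio its main safety test, and the Interim analyses section ties no stopping or safety decision to it. Death is itself a legitimate safety event, and the text says openly that mortality is considered first. The sensitivity analysis is described as a test of event ordering, and it is one. The size of the masking rests on assumed event rates and on the full 6-point benefit.

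Most of this stands. In simulation with all non-fatal events × 1.5 at lower rates, at least one single row flagged harm in 87% of trials, although a row did so in 10% to 14% with no difference at all. A reader might infer that harms would go unreported, that the trial loses its ability to detect them, or that the hierarchy is an error to be removed. The documents support none of these.

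What the reply leaves open is the pooled row itself. Separate rows do not supply a pooled estimate of non-fatal harm, and the only pooled estimate offered mixes that harm with the hoped-for benefit.

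**Conclusion.** The point holds for the composite row and goes no further: that row cannot be read as evidence of no non-fatal harm. At the design effect it absorbs a rise of about 8.7 percentage points in non-fatal events among survivors before it turns neutral, and with no non-fatal difference it would show a significant advantage in roughly half of trials.

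The 8.7 points follow from the plan's mortality rates and the two-tier model. The simulated percentages also depend on assumed event rates and on independence between events. The masking is proportional to the mortality benefit; with equal mortality the composite points the right way, though diluted. At higher event rates a given relative increase is better seen, because its absolute size is larger. Using 14-day rates for a 28-day hospital-mortality tier is a further approximation. This is a cheap improvement to a secondary summary and does not affect the primary analysis.

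**What to change.** Keep the death-first win ratio and the reordered hierarchy. In the Safety events section, describe the win ratio as a benefit-risk summary. Add to that section and to Table 5 one prespecified composite of the non-fatal events only: either the same hierarchy without death, or the proportion with any prespecified non-fatal event, with a risk difference and 95% CI. Show wins, losses and ties by tier so that the share due to death is visible.

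The cost is a few sentences and one or two table rows from data already collected. Recruitment is still under way, so this can be prespecified now.

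There is one downside. Death is a competing event, so if fewer patients die, more remain at risk of a non-fatal event. With an assumed 20% event rate among survivors in both arms, and events counted only in survivors, the proportions over all randomised patients are 0.80 × 20% = 16.0% and 0.86 × 20% = 17.2%, an apparent excess of 1.2 points caused by better survival. The new row should therefore carry a note that it is to be read beside the mortality row.
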